### Power analysis

Analysis of data from the pilot study indicated that the effect of the “Girls on the Go!” program on participant self-esteem was very strong (ie. Change in outcome is 1.5 times the width of the standard deviation). Assuming 80% power, only 10 participants per group will be required in a standard randomised trial with randomisation of individual participants. This study will be a cluster randomised trial however to account for a variance inflation factor (design effect) of 3 (where average size per cluster is n =10, and the ICC is assumed to equal 0.33) then a total of 120 participants in both the primary (n = 60) and secondary (n = 60) schools will be required.

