### Procedure

#### Ethics and trial registration

The randomised control trial was prospectively registered with the Australian and New Zealand Control Trial Registry (ACTR 12610000513011). The trial was conducted in two phases that comprised Study 1 and Study 2.

Study 1 was prospectively registered with the Australian and New Zealand Control Trial Registry (ACTRN12610000513011). We then received notification of further funding to conduct this and Study 2. We submitted an amendment to our ethics application (ethics approval 10119B) to conduct Study 2 with the Monash Health Human Research Ethics Committee as the population of Study 2 and study design only varied slightly from Study 1 (Study 1 involved high school students and had a stepped wedge design of 3 schools being provided with the intervention per term, while Study 2 involved primary school students and had a stepped wedge design of 2 schools being provided with the intervention per term). We then amended the Australian and New Zealand Control Trial Registry so that the sample size listed on the registry was increased from 60 to 120 participants.

#### Study 1

High schools that contacted the Greater Dandenong Community Health Service in 2010 to receive the “Girls on the Go!” program that year were notified of the research and that their school’s placement on the waiting list that year would be determined at random. School welfare officers and teachers forwarded to the Greater Dandenong Community Health Service the list of student names who they determined met the study and program inclusion criteria. An investigator (LT) gained consent from participant’s parents (with assent from the participant) to participate in the research from all referred students. This investigator administered the data collection surveys at baseline and follow-up assessments at the time points indicated (Figures 1 and 2). The program was provided to schools in the order determined by the matched, random allocation sequence.

#### Study 2

The same recruitment and data collection approaches were used for study 2, though with recruitment derived from primary schools, and the addition of one further follow-up assessment.

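### The design effect of 3 does not follow from the stated cluster size of 10 and ICC of 0.33, which give 3.97; the base number per group does not match its inputs either, and the two slips largely offset

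*Protocol article*

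**What the plan says.** The whole calculation stands in the protocol's Power analysis section. The pilot effect on self-esteem is described as very strong: "Change in outcome is 1.5 times the width of the standard deviation". From this the section concludes, "Assuming 80% power", that "only 10 participants per group will be required in a standard randomised trial". It then allows for clustering with a "variance inflation factor (design effect) of 3 (where average size per cluster is n =10, and the ICC is assumed to equal 0.33", and ends with "a total of 120 participants in both the primary (n = 60) and secondary (n = 60) schools will be required".

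Alpha, sidedness and the test are not given. The Participants and setting section puts each school group at 8 to 12 girls. The Design section describes 12 schools, six in each study, in a stepped wedge with all schools crossing to the intervention. The Analyses section plans a three-level mixed model on repeated assessments.

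**The concern.** The cluster size, the ICC and the design effect are printed in one sentence, and they disagree under the standard formula. The design effect is what takes the calculation from 10 per group to 30 per group, and so to 60 per study, so the sample size depends on a figure that its own inputs contradict. The figure before it, 10 per group for 80% power, does not match its inputs either. A reader who judges a null result against the stated 80%, or who reuses an ICC of 0.33 with a factor of 3 to size a similar school-based trial, would be relying on a derivation that does not hold.

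This is not detail that an article would leave to a fuller document. The inputs and the result are both printed.

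**Working it through.** **Inputs from the protocol.** Effect 1.5 SD; power 80%; 10 per group under individual randomisation; cluster size m = 10; ICC = 0.33; design effect 3; 60 per study (all Power analysis). Group size 8 to 12 (Participants and setting). Six schools per study (Design).

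**Assumption.** Two-sided alpha of 0.05, because none is stated.

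**1. The plan's own figure.** 10 per group × 3 = 30 per group; 2 × 30 = 60 per study; 2 × 60 = 120 in all. The total reproduces as a product.

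**2. The design effect.** DE = 1 + (m − 1) × ICC.
- m = 10, ICC = 0.33: 1 + 9 × 0.33 = 3.97.
- m = 8: 1 + 7 × 0.33 = 3.31. m = 12: 1 + 11 × 0.33 = 4.63. No group size in the stated range gives 3.
- DE = 3 at m = 10 needs ICC = 2/9 = 0.22. DE = 3 at ICC 0.33 needs m = 1 + 2/0.33 = 7.1.
- (m − 1) × ICC alone is 2.97, so the leading 1 may have been left out. That is a guess at the cause.

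**3. The plan's chain with 3.97.** 10 × 3.97 = 39.7 per group; 2 × 39.7 = 79.4, about 80 per study.

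**4. The base of 10 per group.** The normal formula is n = 2 × [(1.96 + 0.84)/1.5]² = 6.98, so 7 per group. Power by two-sample t-test at 1.5 SD:

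| n per group | Power (t-test) |
|---|---|
| 7 | 73.1% |
| 8 | 79.7% |
| 9 | 84.8% |
| 10 | 88.7% |

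So 80% needs 7 (normal) or 9 (t-test; 8 falls just short). Ten per group gives 88.7% by t-test or 91.8% by the normal formula.

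**5. Both steps corrected, starting from 1.5 SD and 80% power.**
- Normal: 2 × 7 × 3.97 = 55.6, about 56 per study.
- t-test, fractional n of 8.06: 2 × 8.06 × 3.97 = 64.0 per study.
- t-test, whole n of 9: 2 × 9 × 3.97 = 71.5, about 72 per study.

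The planned 60 lies inside this range of 56 to 72.

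**6. Power of 60 per study at 3.97.** The effective number per group is 30/3.97 = 7.56, against the 10 intended. The noncentrality is 1.5 × √(7.56/2) = 2.92.

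| Method | Power |
|---|---|
| Normal | 83.0% |
| t, 58 df | 81.8% |
| t, df from effective sample (13.1) | 77.0% |

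**The case against.** The strongest reply is that nothing of substance turns on the slip. The base number is too large for 80%, the design effect is too small for its inputs, and the two roughly cancel. The mixed model will estimate the clustering from the data whatever was assumed at sizing. This stands as far as consequences go. It does not make 3 the design effect for 10 girls and an ICC of 0.33, and a near-cancellation that the text does not mention is not a justification for 80%.

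Three stronger readings are tempting, and the documents do not support them.

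- **That 60 per study fails for 80% power and 80 are needed.** The 80 keeps a base of 10 that the stated effect does not require. With both steps corrected, 60 falls on either side of 80% according to the test and an alpha that is not stated.
- **That power is really about 60%.** A t-test on 3 versus 3 school means (4 df) gives 59.6% at 3.97, but it already gives 71.1% at a design effect of 3, so most of the gap to 80% is a separate few-clusters question. That test is not the planned analysis, and 3 versus 3 does not describe Study 2, where two schools start in each of three terms.
- **That the registered increase rests on this factor.** The Ethics and trial registration section says the registry was amended "so that the sample size listed on the registry was increased from 60 to 120 participants" after further funding allowed Study 2 to be added. The doubling reflects a second study.

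A further point stands against printing any single corrected power as final. The formula is for a parallel comparison at one assessment, while this trial has a baseline and repeated follow-up with every school crossing over. If school effects are stable over time, within-school comparison raises power well above the parallel figure. A generalised least squares check assumed three assessments in Study 1 and four in Study 2, fixed time effects, 10 girls per school, ICC 0.33 and constant school effects. It gave at least 98.9% power in Study 1 and 99.9% in Study 2, even on 4 df. With an assumed between-period school correlation of 0.5, Study 1 gave 71% to 76% on 4 df or 92% to 95% by the normal formula. The protocol does not give these correlations, so the figures show only how far the parallel formula may be from the actual design.

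**Conclusion.** Wrong as written. The stated cluster size and ICC give a design effect of 3.97, about a third above the printed 3, and no group size of 8 to 12 gives 3 at that ICC. This part rests on no outside assumption. The base of 10 per group is also inconsistent with 1.5 SD and 80% power, assuming two-sided 5%.

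The effect on power is small as far as the document allows it to be judged: about 77% to 83% for 60 per study by the plan's own parallel-cluster method, against a stated 80%. The derivation needs correcting, but neither inadequate power nor a need for more girls or schools has been shown.

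**What to change.** Keep 60 per study, and in the Power analysis section:

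1. State a design effect of 3.97 for 10 girls per school and ICC 0.33. If 3 was intended, state ICC 0.22 as the assumption instead.
2. Correct the base number per group for 1.5 SD and 80% power (7 by the normal formula, 9 by t-test, at two-sided 5%), and state the alpha, the sidedness and the test used.
3. Replace the statement that 60 per study is what 80% power requires with the power that 60 gives on the corrected inputs. With 3.97 and two-sided 5%, that is about 77% to 83% by the parallel-cluster formula. Add that this formula ignores the stepped-wedge repeated assessments, or recompute the power for the stepped-wedge design and state the correlations assumed.

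Items 1 to 3 cost a few words and numbers. The recomputation, if chosen, is a short piece of statistical work. No sample size, school count or analysis changes.

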## Discussion

Low self-esteem and its associate health consequences such as body dissatisfaction and eating disorders are important societal, cultural, familial and individual matters. They demand urgent attention, greater resources and evidenced based approaches to both assist young people, and girls in particular with low self-esteem and body image concerns and to prevent others from its development. High self-esteem is known to be a protective factor against the development of body dissatisfaction, and disordered eating and therefore this project may have the potential to contribute to the field of prevention of disordered eating. “Girls on the Go!” was developed to deal with these particular issues. To our knowledge this is the first group-based, professional-led, targeted program conducted outside the school environment amongst school age young people with such culturally diverse backgrounds to be evaluated.

This research will enable clinicians to evaluate a new community preventative intervention and thus to apply research into clinical practice. Before the expansion of “Girls on the Go!” it should be subjected to evaluation to demonstrate that it does achieve its objectives. These findings will indicate if the “Girls on the Go!” program may be successfully used and applied in a culturally diverse community and with disadvantaged participants. The results of the two individual studies will allow for comparison of the intervention’s effect at various age groups (i.e. primary school vs secondary schools age young women). Furthermore, “Girls on the Go!” targets girls who have diverse body shapes and sizes and this control trial results will indicate if a holistic approach focused on self-esteem will lead to overall improved health and wellbeing. Therefore, these findings will support a relatively new paradigm shift where self-esteem enhancement and overall health and well-being are emphasized and used as a prevention strategy and it will potentially support the notion that improving self-esteem would lead to improved self-efficacy and body satisfaction in young women (O’Dea and Maloney, 2000; O’Dea, 2005, 2000b; Bacon and Aphramor, 2011).

Information collected by the present research, that documents the development of a preventative intervention originated from a health service delivery, and evaluation of these data, will contribute new information to the field of prevention of eating disorders and health promotion delivery.

## Authors’ original submitted files for images

Below are the links to the authors’ original submitted files for images. Authors’ original file for figure 1 Authors’ original file for figure 2
